### Plans to promote participant retention and complete follow-up {18b}

Study follow-up visits are combined with the regular visits at the rheumatology outpatient clinic to minimize patient burden. The primary outcome is set at 3 months after the intervention, after which anti-rheumatic treatment can be adjusted, discontinued or initiated as usual. All questionnaires can be completed digitally within a 14-day timeframe.

### Data management {19}

Data and questionnaires will be collected using the eCRFs in Castor EDC [30]. The eCRFs are only accessible for investigators and authorized administrators using a password. New data entries and changes made to the eCRF are logged in order to reproduce study steps. Written informed consent forms will be stored in a locked safe in the Maasstad Hospital. All study data will be archived for 15 years after the study has ended.

### Confidentiality {27}

The handling of personal data will comply with the General Data Protection Regulation (in Dutch: Algemene Verordering Gegevensbescherming (AVG) and Uitvoeringswet AVG (UAVG)) and the privacy regulations of the Maasstad Hospital. Patients will be assigned a code number which is used in the eCRF. Only these code numbers will be used in study documentation, reports and publications. The main investigator and study coordinating investigator are the only ones who possess a code key. Other persons or authorities that are allowed access to the code key are the members of the Independent Ethics Committee of the Maasstad hospital. The study monitor appointed by the sponsor, members of the research team and the Health Inspection. This might be necessary to inspect the accuracy and quality of the study.

### Plans for collection, laboratory evaluation and storage of biological specimens for genetic or molecular analysis in this trial/future use {33}

Blood samples and arthroscopically removed synovial tissue will be encoded and stored in the Maasstad Hospital tissue bank. The main investigator is the only one with access to the samples. Analysis of tissue samples will be performed in a later phase and as not part of this study. Analysis includes histological (microscopic) examination, proteomics for identification of inflammatory mediators (e.g. TNF, IL-17A and IL-23) and molecular characterization using single-cell (sc) RNA sequencing. At least five collected tissue samples will be snap frozen to − 80 °C and five will be stored in an RNA stabilizing solution (RNAlater). Blood samples will be investigated using proteomics and RNA sequencing for comparison. For this purpose, approximately 80 ml of blood will be needed at baseline, drawn simultaneously with the regular blood tests. Blood will be stored in heparinized tubes and PAXgene blood RNA tubes (BD Biosciences).

## Statistical methods

### Statistical methods for primary and secondary outcomes {20a}

The primary analysis will be performed according to the intention-to-treat principle. A per-protocol analysis will also be conducted accounting for possible cross-over patients. A description of the planned intention-to-treat and per-protocol analyses for outcome PRWE conform to the estimands framework is provided as a supplementary file [42, 43]. Baseline patient characteristics will be analysed using simple descriptive statistics. Differences in the change in the primary outcome (PRWE at 3 months minus PRWE at baseline) between the two groups will be analysed using a linear mixed model, including the baseline measurement in the outcome vector and stratification variable disease (RA/PSA), time and treatment × time interaction as covariates. The difference in the change in PRWE score will be considered statistically significant if *p* < 0.05 (likelihood ratio test). The model will be extended by including the other time points to assess further trends in the development of PRWE scores. The secondary outcomes, EULAR response rate, DAS28 scores, EQ-5D-5L scores, range of motion (ROM), grip strength and pain (NRS) will be analysed in a similar manner. Differences between the two treatment groups in rates of complications and secondary interventions will be analysed using Pearson’s chi-square test or Fisher’s exact test. IBM SPSS (version 23.0, Chicago, IL) or similar software will be used for analysis.

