### Sample size {14}

The sample size was calculated for the primary endpoint, the difference in PRWE scores at 3 months. According to one study, the median PRWE score in RA patients is 20.0 (IQR: 9.8–48.3) for the dominant hand and 22.8 (IQR 6.9–38.6) for the non-dominant hand, but means and standard deviations for RA are not known [27]. The mean PRWE score among the general population was estimated as 7.7 with a standard deviation of 15.0 [28]. The minimal clinically important difference of the PRWE is 11.0 points [29]. We hypothesize that a mean difference of at least 11.0 points on the PRWE score could be encountered between the two groups after 3 months. A simulation study using *K* = 1000 random draws per sample size from a multivariate normal distribution was performed to estimate the power for several sample sizes, where the significance of the treatment effect was estimated by a linear mixed model (likelihood ratio test). Assuming a (conservative) correlation of 0.1 between PRWE at baseline and at 3 months and a standard deviation of 15.0, it was found that at *α* = 0.05 and power of 90%, 38 patients per treatment arm would be required. To correct for the expected loss to follow-up of 5%, 40 patients in each arm will be included.

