### Sequence generation {16a}

Randomization will be performed using a computerized randomization procedure in Castor EDC [30]. Patients will be randomized in a 1:1 ratio using variable block sizes of two, four and eight patients, stratified for disease type (RA or PSA) to avoid imbalances between groups. The order of the block sizes is unknown to the researchers.

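### The primary mixed model has baseline PRWE as an outcome but disease only as a main effect, so an RA-PsA difference in change goes into the residual and slightly inflates the model-based SE

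*Protocol article*

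**What the plan says.** Under Statistical methods for primary and secondary outcomes {20a}, the change in PRWE from baseline to 3 months is analysed by a linear mixed model "including the baseline measurement in the outcome vector and stratification variable disease (RA/PSA"), with "time and treatment × time interaction as covariates". An interaction with time is written out for treatment and none for disease. The test is a likelihood ratio test at the 5% level. The model is later extended to the other visits. DAS28, EQ-5D-5L, range of motion, grip strength and pain are to be handled similarly.

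Sequence generation {16a} states that randomisation is "stratified for disease type (RA or PSA) to avoid imbalances between groups". The section on additional analyses {20b} plans a PRWE subgroup analysis by RA or PsA. Sample size {14} assumes a "correlation of 0.1 between PRWE at baseline and at 3 months and a standard deviation of 15.0" and an 11-point difference, and gives "power of 90%, 38 patients per treatment arm would be required". No PsA share and no RA-PsA difference in change is stated. Section {20a} refers to a supplementary file describing the estimands, which is not shown.

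**The concern.** A disease term does different work in two common models. With month-3 PRWE as the outcome and baseline as a covariate, it adjusts the month-3 value. With baseline inside the outcome vector, a disease main effect has one coefficient for both visits, so the fitted RA-PsA gap is the same at baseline and at month 3. The quantity of interest here is change, and a constant gap cancels from change.

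The listed model therefore assumes that the two diseases change by the same amount for a given treatment. The protocol gives no support for that assumption, and its planned subgroup analysis by disease treats a different course as possible. If the diseases do change differently, the difference enters the residual covariance and the reported standard error of the treatment effect is larger than it needs to be. What is at stake is a little power and a slightly wide confidence interval.

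**Working it through.** **Inputs.** From Sample size {14}: effect 11, SD 15 at both visits, correlation ρ = 0.1, n = 38 per arm. Assumed, because the protocol gives neither: PsA share p, and RA-PsA difference in change g.

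**1. The protocol's own figure.** With baseline means shared across arms, the relevant variance is 225 × (1 − 0.1²) = 222.75.
- n per arm = 2 × (1.960 + 1.282)² × 222.75 / 11² ≈ 38.7, so 39, against the stated 38.
- SE at 38 per arm = √(2 × 222.75 / 38) = 3.424, and power = Φ(11/3.424 − 1.960) = Φ(1.253) = 89.5%.
- Simulating the maximum-likelihood (ML) mixed model with the likelihood ratio test (10,000 draws) gave 88.9% at 38 per arm and 90.6% at 40.
- A model with a free treatment main effect would have only about 66% power at 38. The stated size therefore matches the shared-baseline model that {20a} lists.

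**2. Effect of leaving out disease × time.** With equal SDs at both visits, the best common disease shift splits the misfit evenly: −g/2 at baseline and +g/2 at month 3. The fitted covariance in large samples is the true one plus q = p(1 − p)g²/4 on each variance and minus q on the covariance. The model SE is then

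SE = √{(2/38) × [(225 + q) − (22.5 − q)² / (225 + q)]}.

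The estimator's real variance uses the fitted slope b = (22.5 − q)/(225 + q): (2/38) × (225 − 2b × 22.5 + b² × 225).

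For p = 30%:

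| g | q | model SE | true SE | SE with disease × time | ratio of model SE to SE with disease × time | power, as written vs with term |
|---|---|---|---|---|---|---|
| 0 | 0 | 3.424 | 3.424 | 3.424 | 1.000 | 89.5% vs 89.5% |
| 10 | 0.21 × 100/4 = 5.25 | 3.471 | 3.425 | 3.424 | 1.014 | 89.0% vs 89.5% |
| 20 | 0.21 × 400/4 = 21 | 3.598 | 3.439 | 3.424 | 1.051 | 87.5% vs 89.5% |

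Power is Φ((11 − 1.960 × model SE)/true SE).

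**3. Other assumptions.** For a PsA share of 10% to 50%, the SE inflation at ρ = 0.1 is 0.7% to 2.0% at g = 11 and 2.8% to 7.0% at g = 22. At an assumed ρ of 0.5 it is 1.8% to 4.8% and 6.7% to 16.4%.

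**4. The planned test at 38 per arm.** Simulation of the ML likelihood ratio test (ρ = 0.1, 30% PsA), as written vs with disease × time:
- g = 10: mean SE 3.37 vs 3.32; power 88.9% vs 89.4%; type I error 4.8% vs 5.1%.
- g = 20: mean SE 3.50 vs 3.32; power 86.7% vs 88.5%; type I error 5.1% vs 5.9%; sampling SD of the estimate 3.44 vs 3.42.

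A second simulation of 4,000 draws per case (Monte Carlo error about 0.35 points) gave type I error of 5.2% vs 5.5% at g = 10 and 4.3% vs 5.5% at g = 20. ML makes the SE about 2% to 4% too small at this sample size, which offsets the inflation.

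**5. Bias.** With balanced strata and complete data, the simulated mean estimate was −10.9 to −11.1 for a true −11. In a deliberately extreme case (5% overall loss, all of it among PsA patients in one arm, 30% PsA, ρ = 0.1), the large-sample estimate was about −11.5 at g = 10 and −11.9 at g = 20 without disease × time, and −11.0 with it. Evenly spread loss gave no bias in either model.

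**The case against.** The strongest reply is that this is a preference. A shared-baseline mixed model with the stratification factor as a covariate is a valid specification. The harm is nil if RA and PsA change alike. A visible loss needs a difference of about 20 points, nearly twice the 11-point minimal important difference, and the protocol stresses the similarity of the two diseases. The supplementary file may also already contain the term. All of this stands and keeps the point minor. It does not remove it: {20a} names the model's terms, and the omitted one concerns the factor used to stratify.

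Four stronger readings are tempting, and the documents do not support them.
- *The stratification is wasted.* Its stated purpose is balance between groups, which is achieved. The estimator's sampling SD is almost the same with or without the term (3.44 vs 3.42 at 20 points).
- *The test becomes conservative whenever the diseases differ.* Under the planned ML test at correlation 0.1, type I error stays near 5%. A clearly conservative test needs both a large disease difference and a higher correlation: the large-sample figure is 2.8% at 22 points, correlation 0.5 and 30% PsA.
- *The treatment effect is biased.* It is not with complete or disease-balanced follow-up. Bias needs loss concentrated by disease and arm.
- *The sample size is wrong.* The stated figure is reproduced to within one patient per arm.

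**Conclusion.** The point holds as a small improvement to the specification. The listed model forces an equal RA-PsA gap at baseline and month 3 and puts any difference in change into the residual. Relative to a model with disease × time, the SE is 1% to 2% too large at an assumed 10-point difference and about 5% at 20 points, costing about 0.5 and 2 points of power. These figures rest on the protocol's SD of 15 and correlation of 0.1, 38 per arm, and an assumed 30% PsA.

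The correlation matters most. The protocol calls 0.1 conservative, and a value well above it makes the relative inflation larger, although power is then also higher (95.8% with the term at 0.5). If the treatment effect itself differs by disease, the average difference in change is half of that difference, and disease × time removes only that average part.

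**What to change.** Add disease × time to the primary model, so that the fixed effects are disease, time, disease × time and treatment × time with a shared baseline. Do the same in the 6- and 12-month extension and in the models for the continuous secondary outcomes. If the supplementary estimand file already has the term, align the text of {20a} with it.

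With the term added, the ML likelihood ratio test runs slightly above 5% at this sample size (5.1% to 5.9% in the simulations above). A test from a REML fit with small-sample degrees of freedom would keep it at 5%; a simulated REML t test gave 5.1% at a 20-point difference.

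The cost is one degree of freedom per follow-up visit and no new data. If the diseases change alike, nothing is lost: power under the REML t test was 88.1% with or without the term. The change should be dated before the analysis.

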### Methods for additional analyses (e.g. subgroup analyses) {20b}

Subgroup analyses with regard to the PRWE score will be performed on type of pathology (RA or PsA), gender and age (18–65 years and > 65 years). Values of *p* < 0.05 will be considered statistically significant.

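### The likelihood ratio test that decides the primary outcome has a true error rate of about 5.5–5.6%, not 5%, at 76–80 patients; an F test from the same model would hold 5% for about one point of power

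*Protocol article*

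**What the plan says.** Section {20a} compares the change in PRWE from baseline to 3 months with a linear mixed model, "including the baseline measurement in the outcome vector and stratification variable disease (RA/PSA), time and treatment × time interaction as covariates". No treatment main effect is listed, so the arms share a baseline mean. The difference is significant at p < 0.05, and the test is named: "likelihood ratio test). The model will be extended by including the other time points". Most secondary outcomes, including DAS28, EQ-5D-5L, range of motion, grip strength and pain, are to be handled similarly.

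Section {14} relies on the same test for power: "the significance of the treatment effect was estimated by a linear mixed model (likelihood ratio test". Its inputs are a difference of 11.0 points, a "correlation of 0.1 between PRWE at baseline and at 3 months and a standard deviation of 15.0", and its result is "0.05 and power of 90%, 38 patients per treatment arm would be required", raised to 40 per arm for 5% loss to follow-up.

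Section {20b} adds: "Subgroup analyses with regard to the PRWE score will be performed on type of pathology (RA or PsA), gender and age". It sets p < 0.05 there too, without naming a test or giving subgroup sizes.

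**The concern.** A likelihood ratio test on a fixed effect compares two maximum-likelihood fits and refers the result to chi-square. Maximum likelihood estimates the residual variance without allowing for the fitted coefficients, and the chi-square reference ignores that this variance is estimated. Both push the p-value down in a trial of this size. The plan states α = 0.05 and then names a test that does not quite deliver it.

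At stake is a borderline result. The trial is open-label with a patient-reported primary outcome, so a p-value just under 0.05 would be looked at closely, and it should not owe its position to an approximation.

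**Working it through.** **Inputs.** From section {14}: difference 11.0, SD 15.0, correlation 0.1, α = 0.05, 38 evaluable patients per arm (N = 76), 40 per arm randomised (N = 80). From section {20a}: the model and the test.

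**Reproducing the plan's figure.**
- Plain two-sample formula: 2 × (1.960 + 1.282)² × 15² / 11² = 39.1, so 40 per arm.
- Allowing for baseline, multiply by 1 − 0.1² = 0.99: 38.7, so 39 per arm.
- Loss to follow-up: 38 / 0.95 = 40 per arm.
- An unadjusted change-score comparison would need 71 per arm, so that is not what was simulated.

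Power of the likelihood ratio test at 38 per arm is 89.2% semi-analytically (noncentral F averaged over baseline imbalance) and 89.1% by simulation (6,000 runs). The plan used 1,000 draws, whose standard error near 90% is √(0.9 × 0.1 / 1000) = 0.9 points. The stated 38 per arm is therefore reproduced.

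**True level of the test.** Take complete data, two time points, a common baseline mean and, for the closed form, no disease term. The likelihood then splits into a baseline part that is free of treatment and a regression of month 3 on baseline and treatment. This gives

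LRT = N × ln(1 + t² / (N − 3)), with t on N − 3 degrees of freedom under the null.

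Setting LRT = 3.841 and N = 76: t² = 73 × (exp(3.841/76) − 1) = 3.785, so |t| = 1.945. The correct cut-off on 73 degrees of freedom is 1.993. The probability beyond 1.945 is 5.56%.

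Simulated levels are from 20,000 runs per size, maximum likelihood, with disease in the model and an assumed 30% of patients in the smaller disease stratum:

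| N | Formula | Simulated, unstructured covariance | Simulated, random intercept | Small-sample F |
|---|---|---|---|---|
| 76 | 5.56% | 5.58% | 5.5% | 4.9% |
| 80 | 5.53% | 5.60% | 5.5% | 5.0% |
| 40 (assumed subgroup) | 6.1% | – | – | – |
| 20 (assumed subgroup) | 7.5% | 8.0% | 7.1% | 5.0% |

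The Monte Carlo standard error at 5% is √(0.05 × 0.95 / 20000) = 0.15 points. The F column is the equivalent baseline-adjusted regression with N − 4 degrees of freedom, standing in for a Satterthwaite or Kenward-Roger test.

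**Intervals.** 1.945 / 1.993 = 0.976, so an interval inverted from the test is about 2% too narrow.

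**PRWE scale.** The standard error is about 15 × √0.99 × √(2/38) = 3.42. The smallest significant difference is 1.945 × 3.42 = 6.66 points instead of 1.993 × 3.42 = 6.82, a gap of 0.16 points.

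**Power, likelihood ratio test against F (semi-analytic).** At 38 per arm: 89.2% against 88.3%. At 40 per arm: 90.6% against 89.9%. Simulation of the F test gives 88.1% and 89.2%. About 41 complete patients per arm are needed for 90% with F, against 39–40 with the likelihood ratio test.

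**The case against.** The strongest reply is that the effect is immaterial. The boundary moves by 0.16 points on a 0–100 scale where the plan's minimal important difference is 11, and only a result whose exact p lies between 0.050 and 0.056 changes verdict. That is correct, and it is why the point is minor.

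A second reply is that estimation method and degrees of freedom belong in an analysis plan, that this article condenses a longer protocol, and that the test is standard and used consistently for both power and analysis. The consistency is real, and silence on REML or degrees of freedom would not be a finding. But the article does name the deciding test and its level, and the two do not match at this size.

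A third reply concerns subgroups, and it stands. A reader might infer from section {20b} that the subgroup tests run at 6–7.5%. The document does not support that: it names no test there, and 40 and 20 patients are assumptions. A treatment-by-subgroup interaction fitted to all patients would show roughly the overall excess.

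A reader might also suspect that the likelihood ratio test is applied to REML fits, where it would be invalid for fixed effects. Nothing in the article says so. Maximum likelihood is the natural reading.

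**Conclusion.** The point holds, and it is small. The stated rule has a true two-sided error rate of about 5.5–5.6% with 76–80 patients, an excess of 0.5–0.6 percentage points, and intervals inverted from it are about 2% too narrow. Continuous secondary outcomes tested the same way share this. A higher rate within subgroups is conditional on the same test being run inside them.

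The result assumes maximum-likelihood fitting, normal data and complete follow-up to month 3. The covariance structure is not stated, but both structures tried lead to the same conclusion. The figures do not show that the sample size is wrong: 38 per arm is reproduced for the test the plan names. Nor is the alternative free, because it gives up about one point of power, most of which reflects the likelihood ratio test's inflated level.

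**What to change.** Keep the model and replace the named test in section {20a} with wording such as: *The model is fitted by REML. The p-value and 95% confidence interval for the treatment × month-3 coefficient come from an F (t) test with Satterthwaite or Kenward-Roger degrees of freedom. The same applies to continuous secondary outcomes and to treatment-by-subgroup interaction terms.*

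In section {14}, restate power for that test as about 88% with 38 evaluable patients per arm and about 90% with 40, or rerun the simulation with it.

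The cost is about one point of stated power. To keep a full 90% on evaluable patients, one to two more complete patients per arm would be needed than with the likelihood ratio test. The design, visits and estimand do not change.

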#### Secondary outcomes

The following secondary outcome measures will be measured at baseline, 3 months, 6 months and 12 months (Table 1):Range of motion (ROM) of the wrist measured using a standard goniometer, including pronation, supination, ulnar and radial deviation, and palmar and dorsal flexionGrip strength of the wrist measured using a dynamometer (Saehan). Grip strength will be calculated as the mean of three attemptsNumeric Rating Scale (NRS) pain scale. A score of 0 indicates no pain, and a score of 10 indicates the worst possible painEULAR response rate and Disease Activity Score (DAS28)Resolution of synovitis measured by wrist ultrasound in grey scale and power Doppler mode (baseline and 3 months only)Wrist arthritis and joint destruction on standard (plain) radiographs of the wrist (baseline and 12 months only)Quality of life measured with the EuroQol 5D (EQ-5D-5L) questionnaireBlood parameters including erythrocyte sedimentation rate (ESR) and C-reactive protein (CRP) (part of the routine clinical care)Complications and subsequent treatment

**Table 1 Tab1:** Trial schedule according to the recommendation for interventional trial (SPIRIT) guidelines

	Enrolment	Allocation	Post-allocation					
Timepoint**	*14 days (*± *4 days) prior to intervention*	Intervention	*Week 2*	*Week 4*	*Week 6*	*Month 3*	*Month 6*	*Month 12*
Enrolment								
Eligibility screen	X							
Informed consent	X							
Allocation	X							
Interventions								
Arthroscopic synovectomy		X						
Intra-articular corticosteroid injection		X						
Assessments								
Questionnaires (PRWE, EQ-5D-5L, iMCQ, iPCQ)	X					X	X	X
Physical exam (including ROM, GS and DAS28)	X					X	X	X
Wrist ultrasound	X					X		
Plain wrist radiographs	X							X
Blood parameters (ESR, CRP)	X					X	X	X
NRS pain scores	X		X	X	X	X	X	X
Complications and secondary treatment			X	X	X	X	X	X
Cost-effectiveness analysis								X

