Secondary outcomes include the EULAR response rate, reduction of synovitis on wrist ultrasound, progression of wrist arthritis on plain radiography and quality of life. DAS28 scores are used to determine the EULAR response rate, which measures responsiveness to anti-rheumatic treatment. The DAS28 is a composite measure of disease activity in rheumatic patients calculated by evaluating 28 joints for swelling and tenderness, combined with NRS pain scores and C-reactive protein levels in the blood. Wrist ultrasound, performed by one of two experienced rheumatologists, is used to measure the resolution of synovitis and is scored using the EULAR-OMERACT combined scoring system which combines grey scale and power Doppler mode [33]. Ultrasound has demonstrated greater sensitivity than clinical assessment and conventional radiography for detecting synovitis in RA target joints [34, 35]. Standard wrist radiographs will be graded using the modified Larsen grading system, which scores degenerative wrist arthritis and joint destruction on a score of 0 to 5, 5 indicating the most joint abnormalities [36, 37]. The EuroQol 5D (EQ-5D-5L) questionnaire is a widely used standardized questionnaire scoring overall quality of life using five different 5-level domains, on a scale from 0 to 100. It has been validated and translated to Dutch [38, 39]. A cost-effectiveness analysis will be performed based on medical costs and productivity loss (see the ‘Methods for additional analyses (e.g. subgroup analyses) {20b}’ section). The iMTA Productivity Cost Questionnaire is a standardized instrument for measuring and valuing health-related productivity losses and estimated societal costs based on educational level, job type and lost workdays [40]. The iMTA Medical Consumption Questionnaire (iMCQ) is a standardized instrument including questions related to frequently occurring contacts with health care providers, medication use and home care [40]. Medical resource prizes will be obtained from the Dutch Healthcare Authority [41]. From these costs, cost-effectiveness will be calculated in relation to quality-adjusted life years (QALYs) using the EQ-5D-5L (or PRWE) over a 1-year and 5-year span.

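### EULAR response is assigned to the PRWE linear mixed model, which needs a baseline value that a response measure does not have

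*Protocol article*

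**What the plan says.** All of this is in the Protocol article.

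- **Statistical methods {20a}, reference model.** Change in PRWE is analysed with a linear mixed model "including the baseline measurement in the outcome vector and stratification variable disease (RA/PSA), time and treatment × time interaction as covariates", with a likelihood ratio test. No treatment main effect is listed.
- **Same section, secondary outcomes.** "EULAR response rate, DAS28 scores, EQ-5D-5L scores, range of motion (ROM), grip strength and pain (NRS) will be analysed in a similar manner".
- **Same section, rates.** A categorical test is named, but for other outcomes: "rates of complications and secondary interventions will be analysed using Pearson’s chi-square test or Fisher’s exact test".
- **Plans for assessment {18a}, nature of the outcome.** "DAS28 scores are used to determine the EULAR response rate, which measures responsiveness to anti-rheumatic treatment".
- **Secondary outcomes, timing.** The list opens with "The following secondary outcome measures will be measured at baseline, 3 months, 6 months and 12 months" and includes EULAR response and DAS28 as one combined item.

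**The concern.** The reference model has two features that matter here. It is linear, and it treats the baseline measurement as the first of the repeated outcomes, so that the treatment × time term estimates a difference in change. Both require an outcome that exists before treatment on the same scale as afterwards. A measure of response to treatment does not: it is judged against the pre-treatment state.

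An analyst who follows the sentence must therefore either invent a baseline value, most naturally non-response for everyone, or depart from the stated model. The first route puts a constant into the outcome vector and can distort the standard error. The second leaves the choice of coding and model open until the data are in hand. At stake is the reliability of the p-value for one named secondary efficacy outcome.

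**Working it through.** **Step 1. Is there a figure to reproduce?** The article gives none for EULAR response. The PRWE sample size does help to identify the reference model. Inputs from Sample size {14}: difference 11.0, SD 15.0, correlation 0.1, α = 0.05 (two-sided assumed), power 90%, 38 per arm. With (1.960 + 1.282)² = 10.51:

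- Baseline in the outcome vector with a common baseline mean: n = 2 × 10.51 × 225 × (1 − 0.1²) / 121 = 38.7, so 39 per arm. Simulated power of the likelihood ratio test at 38 per arm is 89.3%.
- Plain change score: n = 2 × 10.51 × 225 × 2(1 − 0.1) / 121 = 70.4, so 71 per arm.

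The stated 38 fits the first model and not the second. This agrees with the covariate list: baseline is an outcome, and the arms share one baseline mean. It is the model that EULAR response inherits.

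**Step 2. Does each listed outcome fit?** DAS28, EQ-5D-5L, range of motion, grip strength and NRS pain are scores recorded at baseline and at follow-up, so they fit. EULAR response is derived from DAS28 scores to express response to treatment. It has no pre-treatment value and does not fit.

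**Step 3. What happens if the model is fitted anyway?** Assumptions, none of them in the documents:

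- binary response with the same true rate p in both arms;
- 38 per arm with complete data;
- every patient coded 0 at baseline;
- fixed effects for time and treatment × time only, with the RA/PsA stratum left out for simplicity;
- one common residual variance and zero random-intercept variance.

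The baseline residuals are all zero, so averaging over both visits halves the residual variance, from p(1 − p) to p(1 − p)/2. At p = 0.45:

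- p(1 − p) = 0.2475, and the pooled value is 0.1238.
- Appropriate standard error of the difference: √(2 × 0.2475 / 38) = 0.114.
- Model standard error: √(2 × 0.1238 / 38) = 0.081.

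The ratio is √2, so the test in effect rejects at |Z| > 1.960 / 1.414 = 1.386. That has a large-sample probability of 16.6% under the null. Simulated likelihood ratio tests (40,000 null trials at each rate), which also reflect the discreteness of the data, reject in 17% to 20% of trials at p = 30%, 45% and 60%. Using follow-up values only, they reject in about 5%.

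**Step 4. How far does this depend on the implementation?** Add a treatment main effect. The contrast then involves four cell means, and its standard error is √(4 × 0.1238 / 38) = 0.114, which is the appropriate value. Simulated rejection returns to 5% to 6%.

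In both versions the point estimate is the difference in response proportions, because the baseline cells are all zero.

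**The case against.** **Similar is not identical.** The wording may allow a mixed model with a link suited to the outcome, such as a logistic or ordinal one. This is fair as regards linearity. It does not help with baseline: a generalised mixed model still has no baseline response to include, and no change in response for treatment × time to estimate.

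**An article condenses the full protocol, and an analysis plan may exist.** Those documents could settle coding and link function. But the point is not that detail is missing. The article assigns a method, and the method does not fit. The supplementary estimand file is described as covering PRWE only.

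**The response categories are not defined in the article.** That is true, and it is why the choice between a binary and an ordinal analysis should stay open here. That response is judged against the pre-treatment state follows from the article's own description.

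**Stronger readings that a reader might infer.** One is that the analysis cannot be run, is degenerate, or yields an effect without meaning. The documents do not support this. At least one version runs, its estimate is a risk difference under binary coding, and the article states no covariance structure. Another is that the plan carries a false-positive rate near 20%. That belongs to one implementation under assumed inputs. A third is that the Secondary outcomes section wrongly schedules a baseline EULAR response. It is a combined item with DAS28, which must be measured at baseline, under a general lead-in; Table 1 schedules only DAS28. That wording needs at most an editorial tidy-up.

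**The consequence is small.** This stands. DAS28 itself has a suitable analysis.

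**Conclusion.** The point holds as a minor correction. The article places EULAR response under a linear model of change with baseline in the outcome vector, and by its own description the measure has no baseline value. The mismatch rests on the text alone.

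Its size depends on how the sentence is carried out. With non-response coded for all at baseline, the listed fixed effects and a common variance, the test is anti-conservative: roughly 17% to 20% instead of 5% at assumed response rates of 30% to 60%. With a treatment main effect the excess largely disappears. One secondary outcome is affected. The primary PRWE analysis and the sample size are not.

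**What to change.** In Statistical methods {20a}, remove EULAR response from the list of outcomes analysed like PRWE. State that it is compared at follow-up visits only (3, 6 and 12 months) with a categorical method, for example logistic or proportional-odds regression adjusted for the RA/PsA stratum and baseline DAS28, and that the risk difference at 3 months is reported. Other categorical methods would also serve; what matters is to name one before analysis. Keep the linear mixed model for DAS28, EQ-5D-5L, range of motion, grip strength and NRS pain. Optionally, note in Secondary outcomes that EULAR response applies to follow-up visits only.

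Cost: one sentence, no new data, and no effect on sample size or visit schedule.
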